**Methods/design:**

Our study is a secondary analysis for the database from ATTEMPT study, enrolling 560 ST-segment elevation myocardial infarction (STEMI) patients undergoing pPCI. Patients will be divided into 2 groups according to the admission serum uric acid (SUA) level. Hyperuricemia will be defined as a SUA level > 7 mg/dL (417 mmol/L) in males and > 6 mg/dL (357 mmol/L) in females. The primary endpoint was CI-AKI, defined as > 25% or 0.5 mg/dL increase in serum creatinine from baseline during the first 48–72 h post-procedurally. Multivariate analyses for CI-AKI and long-term mortality will be performed using the logistic regression and Cox regression analyses, respectively.

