## Methods/design

### Study design and population

This is a secondary analysis of aggressive hydration in patients with STEMI undergoing pPCI to prevent contrast-induced nephropathy, the first study for reduction of contrast-induced nephropathy following cardiac catheterization (ATTEMPT RESCIND-1 study). Five hundred sixty patients aged 18 years or older, treated with pPCI, and provided written informed consent were included from 15 medical research centers in China. Inclusion and exclusion criteria were described elsewhere [19]. We also excluded the patients without the admission serum uric acid (SUA) level.

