### Study protocol

Baseline data will include demographics, diagnosis, medical history, laboratory parameters, medications, and physical examination. Patients will be divided into 2 groups according to the admission serum uric acid (SUA) level. Hyperuricemia will be defined as a SUA level > 7 mg/dL (417 mmol/L) in males and > 6 mg/dL (357 mmol/L) in females. The comorbidities will include hypertension, diabetes mellitus, hyperlipidemia, heart failure, chronic kidney disease, stroke, peripheral arterial disease, and chronic obstructive pulmonary disease. The concomitant therapies were decided by the doctors and were relied on the routine standards of care recommended by the current guidelines. The primary outcome, CI-AKI, was defined as a 25% or 0.5 mg/dL increase in serum creatinine from baseline at 48–72 h after pPCI [19]. The secondary endpoints were different definitions of CI-AKI, persistent renal impairment, major adverse clinical events during hospitalization, total hospitalization costs, and length of hospital stay [19].

Follow-up adverse events will be recorded by trained investigators via office visits or telephone interviews at 3, 6, 12, 18, and 24 months after the pPCI. Long-term outcomes will be major adverse cardiovascular events (MACEs), including mortality, stent restenosis, non-fatal myocardial infarction, and target vessel revascularization.

All data will be collected with standardized electronic case report forms. At the time of enrollment, the data management team of Guangdong Provincial People’s Hospital will conduct consistency checks and issues data clarification forms to deal with discrepant data. All data will be collected after the approval by the ethics committee of all participating centers. An independent data monitoring committee will review the ongoing safety events of every participant.

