### Statistical analysis

Baseline patient characteristics and information will be presented as the mean ± standard deviation or median plus interquartile ranges of descriptive statistics. They will be compared by *t* test or Wilcoxon rank sum test according to distribution. The categorical data about baseline characteristics and information will be expressed as a percentage were analyzed using the Pearson chi-square test or Fisher’s exact test. The association between hyperuricemia and CI-AKI will be performed using multivariate logistic regression analysis. Multivariable logistic regression models have been developed to adjust for clinical characteristics (e.g., age, sex, estimated glomerular filtration rate, left ventricular ejection fraction, chronic heart failure, anemia, diabetes mellitus), and the Mehran risk score will be calculated [3]. All variables that are univariately associated with this outcome measure will be entered as possible predictors in a multivariable logistic regression analysis. The association between hyperuricemia with long-term mortality will be investigated by Cox regression model adjusting for other risk factors (e.g., age, CI-AKI, heart function, renal function, and medication). Kaplan-Meier curve and log-rank test will be performed on the survival time of the hyperuricemia group and the normouricemia group (the cumulative rate of all-cause mortality and MACEs between these two groups). These data will be analyzed on the basis of valid cases. A two-tailed *p* value < 0.05 will be considered statistically significant. The power calculation was based on our previous finding [20], and a CI-AKI incidence of 23% was estimated for the hyperuricemia group, while 11.5% was assumed for the normouricemia group (50% relative reduction). Using a two-sided chi-square test, a significance level of 0.05, and a sample size of 280 each group, the power of the tests is over 90%.

All statistical analyses will be performed using SAS version 9.4 or later (SAS Institute, Cary, NC, USA) and R software (version 3.1.2; R Foundation for Statistical Computing, Vienna, Austria).

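### The power of over 90% is correct for 280 against 280 and a crude chi-square test, but it is not supported for cut-off-defined uric-acid groups analysed by adjusted logistic regression

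*Protocol article*

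**What the plan says.** The calculation is in the protocol article, Statistical analysis. It assumes "a CI-AKI incidence of 23% was estimated for the hyperuricemia group, while 11.5% was assumed for the normouricemia group (50% relative reduction"). The test is specified as "Using a two-sided chi-square test, a significance level of 0.05", and the conclusion is "a sample size of 280 each group, the power of the tests is over 90" per cent.

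Three other statements bear on it:

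- **Total sample.** The abstract describes the source database as "enrolling 560 ST-segment elevation myocardial infarction (STEMI) patients undergoing pPCI". Two groups of 280 use up exactly those 560.
- **How the groups arise.** Under Study protocol: "Patients will be divided into 2 groups according to the admission serum uric acid (SUA) level". The cut-off is fixed and sex-specific, above 7 mg/dL in men and above 6 mg/dL in women. No expected prevalence of hyperuricemia is given anywhere.
- **Who is analysed.** Under Study design and population: "We also excluded the patients without the admission serum uric acid (SUA) level". Statistical analysis adds that only valid cases are used.

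The same section tests the link between hyperuricemia and CI-AKI by multivariable logistic regression. Its example covariates are age, sex, eGFR, ejection fraction, chronic heart failure, anemia and diabetes. The abstract's aim is to show that hyperuricemia is an independent predictor.

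**The concern.** The power figure describes a design with two equal groups of preset size, nobody excluded and an unadjusted comparison. The planned study has none of these features. Hyperuricemia is an observed exposure, and a fixed clinical threshold is neither an allocation nor a median split, so the group sizes will follow the prevalence. Some of the 560 will drop out for missing SUA. Adjustment for covariates related to uric acid, such as renal function, costs precision.

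What is at stake is how the result is read. The Discussion itself calls the existing evidence conflicting, so a null adjusted result is possible. It would then be set against a power of over 90% that was never calculated for that analysis.

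**Working it through.** **Inputs from the article:** p1 = 0.23, p2 = 0.115, difference 0.115, two-sided alpha 0.05 (z = 1.96), N = 560.

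**Inputs not in the article, so assumed and varied:** share of patients with hyperuricemia (20% to 50%), squared multiple correlation R² of hyperuricemia with the covariates (0, 0.1, 0.2), and loss through missing SUA or creatinine (0 or 10%).

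**Formula**, two proportions with pooled variance under the null:

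- p̄ = (n1·p1 + n2·p2)/(n1 + n2)
- SE0 = √[p̄(1 − p̄)(1/n1 + 1/n2)]
- SE1 = √[p1(1 − p1)/n1 + p2(1 − p2)/n2]
- power = Φ[(0.115 − 1.96·SE0)/SE1]

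**Step 1: the plan's own figure.** For 280 and 280, p̄ = 0.1725, SE0 = 0.03193 and SE1 = 0.03156. Power = Φ[(0.115 − 0.06258)/0.03156] = Φ(1.661) = 95.2%. With a continuity correction it is 93.9%. For 90% power, 225 per group would be enough. The stated figure is correct for its inputs.

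**Step 2: unequal groups, still crude.** At a 30% share (168 and 392), p̄ = 0.1495, SE0 = 0.03288 and SE1 = 0.03625, so power = Φ(1.395) = 91.8%. At a 20% share (112 and 448), SE0 = 0.03644 and SE1 = 0.04253, so power = 84.7%. The crossing point for 90% is about 26%: 147 against 413 gives 89.9%.

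**Step 3: adjustment.** Multiply both group sizes by (1 − R²) and reuse the formula. At a 30% share with R² = 0.1, the effective sizes are 151.2 and 352.8, SE0 = 0.03466 and SE1 = 0.03821, so power = 89.1%.

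**Step 4: exclusions.** A 10% loss gives N = 504. On its own it has the same effect as R² = 0.1, since both multiply n by 0.9.

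| Share with hyperuricemia (assumed) | N=560, crude | N=560, R²=0.1 | N=560, R²=0.2 | N=504, R²=0.1 | N=504, R²=0.2 |
|---|---|---|---|---|---|
| 50% | 95.2% | 93.0% | 89.9% | 90.3% | 86.6% |
| 40% | 94.5% | 92.2% | 89.1% | 89.5% | 85.8% |
| 35% | 93.5% | 91.0% | 87.7% | 88.1% | 84.3% |
| 30% | 91.8% | 89.1% | 85.5% | 85.9% | 82.0% |
| 25% | 89.1% | 86.0% | 82.1% | 82.6% | 78.4% |
| 20% | 84.7% | 81.2% | 77.0% | 77.5% | 73.1% |

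At N=560, power drops below 90% at a share of about 26% when R² = 0 and about 32% when R² = 0.1. When R² = 0.2 it is below 90% at every share.

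**Step 5: what is held fixed.** The assumed rates imply an odds ratio of (0.23/0.77)/(0.115/0.885) = 2.30. The table carries that crude contrast over as the adjusted effect. If part of it is confounding by renal function or heart failure, the adjusted effect is smaller and power is lower than shown.

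**The case against.** Much of the other side stands. There is no arithmetic error. Imbalance alone does little harm: crude power stays above 90% down to a share of about 26%. Every figure below 90% rests on a prevalence, an R² or a loss that the article does not supply. Method matters at the margin: a Wald test of the log odds ratio at a 30% share and R² = 0.1 gives 90.3%, where the table has 89.1%. Powering on two proportions ahead of a logistic model is a common simplification. The article also says that a statistical scheme is still to be written, and sensitivity to prevalence could sit there. That scheme would not repair the printed claim, however, because its inputs conflict with design features stated in the same article.

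Three stronger readings are tempting, and the documents do not support them.

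- A reader might infer that the power is illusory or the study clearly underpowered. Most scenarios above stay near or over 80%, and several stay over 90%.
- A reader might set the plan against the odds ratio of 1.26 cited in the Discussion. That figure belongs to a cut-off of 5.4 mg/dL, a different exposure, and the Discussion itself notes that definitions were not uniform. The plan did not target that effect.
- A reader might take the phrase about a 50% relative reduction as an error. Half of 23% is 11.5%, so it is numerically right. It suits a treatment better than an exposure, but that is wording only.

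That the groups will not split evenly is likewise an inference. What the text establishes is that nothing in the design makes them equal.

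**Conclusion.** The point holds as a mismatch between the power statement and the planned analysis, and it should be fixed. The text alone establishes three things: equal groups are assumed without a basis, exclusions are ignored, and the test that was powered is not the adjusted analysis planned for the association. The size of the shortfall is conditional. Over assumed prevalences of 20% to 40% and R² of 0.1 to 0.2, power at N=560 runs from 92.2% down to 77.0%. With an assumed 10% loss it runs from 89.5% down to 73.1%. All of this takes the plan's 23% and 11.5% at face value. The consequence is confined to how a null finding is interpreted; the adjusted estimate and its confidence interval are unaffected.

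**What to change.** Remove the statement of 280 per group and over 90% power, and replace it with a paragraph along these lines:

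> The sample size is fixed by the parent trial (560 patients). After excluding patients without an admission SUA or the creatinine values needed for the endpoint, we expect N = [value]. The expected prevalence of hyperuricemia under the study cut-offs is [value], from [source]. For the multivariable logistic model, power [or the minimum detectable adjusted odds ratio at 80% power] is tabulated for prevalences of 20% to 40% and for R² between hyperuricemia and the covariates of 0 to 0.2.

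Use one calculation method throughout the table, and say whether the assumed odds ratio is crude or adjusted.

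The cost is one rewritten paragraph and a short table, with no extra patients and no change to conduct or analysis. The downside is that the stated power becomes somewhat less favourable.

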## Discussion

CI-AKI is closely associated with prolonged hospital stay, long-term morbidity, and mortality in patient undergoing PCI. The incidence of CI-AKI is about 2% in the general population and over 50% in high-risk population [3]. Previous study supported the relationship between CI-AKI and higher incidence of adverse short- and long-term cardiovascular outcomes, including mortality [21]. Patients with STEMI are likely to present with hypotension, or even cardiogenic shock, higher volume of contrast media, and impossibility of renal prophylactic therapy, which are associated with an increased risk of CI-AKI [22].

Advanced age, diabetes, dehydration, hypotension, sepsis, cardiovascular disease, underlying acute kidney injury, chronic kidney disease, and concomitant use of nephrotoxic drugs were identified as well-known risk factors for CI-AKI [3, 23]. In previous studies [6, 7], we reported that hyperuricemia was an independent risk factor for CI-AKI in PCI patients, which was consistent with other studies [8–13]. However, other studies did not show the same conclusion [14, 15]. Several studies explored the effect of serum uric acid (SUA) on CI-AKI among high-risk patients such as STEMI undergoing primary PCI. Elbasan et al. showed that SUA was associated with CI-AKI in STEMI patients undergoing pPCI (mean SUA = 6.2 ± 0.9 mg/dL, 95% CI, 1.877–3.236; *p* = 0.002) [16]. In another study, Mendi et al. demonstrated that SUA ≥ 5.4 mg/dL was an independent risk factor for CI-AKI (OR 1.26, 95% CI, 1.10–1.42; *p* < 0.001) [17]. Saritemur et al. showed that elevated uric acid was lined with CI-AKI in multivariate analysis after adjusting for potential confounding factors (OR 1.01, 95% CI, 1.00–1.01; *p* = 0.01) [18]. However, even though they reported that high SUA was an independent predictor of CI-AKI in STEMI patients, there was no uniform standard for the definition of hyperuricemia. In our study, we will employ the definition consistent with our previous study.

In addition, these studies did not compare the prognosis between CI-AKI group and non-CI-AKI group in STEMI patients undergoing PCI. Some observational studies proved the relationship between hyperuricemia and clinical outcomes in the presence of gout, but not for asymptomatic hyperuricemia [24, 25]. Nevertheless, a recent study by Pagidipati et al., including the PLATO and TRACER study population, demonstrated a significant association between uric acid (UA) and short-term adverse outcomes, independent of the presence of gout [26]. Regarding the relationship between UA and long-term prognosis, the data also supported the relationship between elevated UA and long-term prognosis in patient with acute coronary syndromes and treated with PCI [27]. Therefore, whether hyperuricemia is still a predictor of poor long-term prognosis after adjusting for CI-AKI should be studied in STEMI patients receiving pPCI.

Although the pathophysiological mechanisms of adverse reactions to hyperuricemia have not been fully elucidated, it appears to be multifactorial. In experimental models, hyperuricemia was linked to a variety of proatherogenic processes, including increased oxidative stress [28], vascular smooth muscle cell proliferation [29], inflammation [30], and endothelial dysfunction [31].

### Limitations

Our current secondary analysis is subject to the following restrictions. First, its sensitivity was lower due to the definition of > 0.5 mg/dL because it was less selective for patients with higher risk of mortality and morbidity. Second, single baseline SUA measurements were used to predict CI-AKI and long-term mortality. However, a number of previous studies have used this method as well. Third, the measurement of serum creatinine (SCr) was standardized at 72 h after pPCI rather than at random, which might lead to the ignorance at the increase in delayed SCr (> 72 h). Finally, it is a secondary analysis that is not capable of testifying a causal relationship.

In conclusion, our study will determine the association between hyperuricemia and contrast-induced acute kidney injury (CI-AKI) after primary percutaneous coronary intervention (pPCI) and will identify if hyperuricemia is a risk factor for long-term death after adjusting for CI-AKI.

### Trial status

The first patient was included in the RESCIND –1 ATTEMPT Trial (Protocol version 2.0, 11 June 2014) on 1 July 2014 and expected to complete recruitment in December 2018. As of October 24, 2018, recruitment is ongoing with 555 patients randomized at 15 centers in China.

## Data Availability

Data sharing not applicable to this article as no datasets were generated or analyzed during the current study.

## Abbreviations

CI-AKI: Contrast-induced acute kidney injury
pPCI: Primary percutaneous coronary intervention
STEMI: ST-segment elevation myocardial infarction
SUA: Serum uric acid
SCr: Serum creatinine
